### Qualitative semi-structured interview

An exploratory objective of this study is feasibility. Feasibility will be measured through semi-structured interviews and clinical data, such as impact on duration of visit and wait time. As described in Table 2, semi-structured interviews will be performed with a subset of participants (10–12) and all practice physicians seeing eligible patients (6) to assess feasibility and acceptability of the intervention. Interview participants will be identified through convenience sampling. Semi-structured interviews involve use of open-ended questions and probes to elicit descriptive data. Most studies suggest saturation, or retrieval of no new information, is achieved with 8 participants [41]. In this study, telephone interviews will be conducted approximately 7 days after the participant enrolls in the Trial Library study. Physician interviews will occur in-person after clinic visits or within 7 days of encounter with participant. The interviews will use open-ended questions, and participant responses will be recorded, transcribed, and analyzed using thematic analysis. An analysis of saturation will be performed with two researchers coding transcripts of interviews. The researchers will meet to compare and reconcile code, discuss discrepancies, and achieve consensus on each transcript. If saturation is not achieved, up to 8 additional participants may be recruited for interview.

Moreover, data will be extracted from the real-time locating system for hospitals (RTLS), a location technology platform currently instituted as part of standard of care at HDFCCC. RTLS is a system used to provide immediate or real-time tracking and management of staff and patients. This data will be utilized to evaluate the impact that in-clinic use of the Trial Library tool has on the duration of each clinic visit. These measures will be used to assess the feasibility of this intervention. While in the clinic, all patients and doctors wear a locating sensor which is used to gather data on location and visit duration. Investigators will collect participant wait time and length with provider during clinic visit from the RTLS data. The data gathered for participants will be compared to a historical baseline generated by 66 patients who meet the study eligibility criteria but who presented to the clinic prior to the initiation of this study.

To evaluate if the Trial Library intervention increases clinic length time, a two-sample *t* test will be used to compare minute average of study participants with the reference group (deidentified minute average of new patients seen at HDFCCC prior to initiation of study).

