### Study schema

The study schema is shown in Fig. 1. Potential participants meeting the study eligibility criteria will be identified by the study coordinator through electronic health record review 7 days prior to the clinic appointment. After check-in, all potentially eligible participants will be approached by a study coordinator, introduced to the research study, and asked to provide written informed consent on paper. The Institutional Review Board requires that all study participants be informed of the details of the study including any potential risks or benefits and that informed consent be acquired from each participant before they can be included in the study. This study requires a Health Insurance Portability and Accountability Act (HIPAA) form in order for researchers to access electronic health records and collect participant clinical and sociodemographic information. Informed consent for the survey is required for all participants; however, participants will also have the option to provide informed consent to participate in a qualitative interview. Required and optional consent for patient participation in components of this study are detailed in Table 1. Subsequent to providing informed consent, the participant will be given an iPad. Approached participants may decline to participate in the study and return the iPad to the check-in desk or the study coordinator. Physicians will be approached by a study coordinator to provide written informed consent on paper for a qualitative interview within 7 days of encounter with the study participant.

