### Study intervention

The Trial Library intervention has several components summarized using TiDIER format (Additional file 1) [38]. The first component is visual, audio, and written educational content describing clinical trials. The second component is a matching tool composed of a series of visual questions, such as an image of a human body with separate selections for non-metastatic versus metastatic disease. The last component is a patient report that includes all available trial options, including the technical and plain description of clinical trial name, summary of trial description in plain English, frequency of appointments required for clinical trial, and location of trial. Participants who review the components of the Trial Library intervention will receive a printed copy of a trial matching report and return the iPad to the front desk. At the end of the clinic visit, participants will be asked to complete a post-visit survey regarding their experiences using the Trial Library intervention and interactions with their physicians. A subset of participants will be identified by convenience sampling, and all clinic physicians will be asked to participate in semi-structured interviews about their experiences with the Trial Library intervention by phone or in-person. Table 2 summarizes the interview guide questions, and their associated study themes, that will be used to conduct qualitative interviews with selected participants of this study.

**Table 2 Tab2:** Semi-structured interview guide summary and associated study themes

Question	Feasibility	Acceptability	Efficacy
Patient			
Tell me about your experience using the Trial Library website.	X	X	
What did you learn from using the Trial Library website?		X	X
How did using the Trial Library website influence your visit with your health care provider?	X		X
How did using the Trial Library website influence your interest in participating in clinical trials?			X
Physicians			
Tell me about your experience having the Trial Library pilot study take place in your clinic.	X	X	
What is the clinical value of the Trial Library resource?		X	X
How did using the Trial Library website influence your visit with your patients?	X		X

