### Sample size and justification

The sample size for this study is 66 participants. In the literature, 35% of patients with cancer utilize the Internet as a preferred source of health information over their provider [39]. To our knowledge, there is no data available on satisfaction rate with online health information; therefore, we use 35% as a proxy for satisfaction rate with online health information in this patient population. To measure the overall satisfaction rate of study participants, we will determine the proportion of participants who report some degree of satisfaction on a 5-item Likert scale from extremely dissatisfied to extremely satisfied with the Trial Library intervention by point estimation and its 95% confidence interval and will be compared to a proxy reference satisfaction rate of 35% by one-sample proportion test. In this pilot feasibility study, the null hypothesis that the true satisfaction rate (acceptability) is 35% will be tested against a one-sided alternative. The null hypothesis will be rejected if 29 or more satisfactions are observed in 66 participants. This design yields a type I error rate of 0.0487 and power of 0.8010 when the true satisfaction rate is 50%.

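### The RTLS clinic-time comparison can count study consent and survey minutes as an effect of the tool, because only participants, not the historical patients, undergo them

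*Protocol article*

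**What the plan says.** All places are in the protocol article.

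- **Before the provider (Study schema).** "After check-in, all potentially eligible participants will be approached by a study coordinator". The study is introduced, written consent is sought on paper, and the iPad is handed over only after consent. A HIPAA form is also required; it is described with the consent, but its exact moment is not given.
- **After the provider (Study intervention).** "At the end of the clinic visit, participants will be asked to complete a post-visit survey". The sections on measures and on the quantitative survey confirm that it is done on paper at that point.
- **Measurement (Qualitative semi-structured interview).** "While in the clinic, all patients and doctors wear a locating sensor which is used to gather data on location and visit duration". Of the components, "Investigators will collect participant wait time and length with provider during clinic visit from the RTLS data". The start and end of the visit interval are not defined.
- **Comparator (same section).** The participants' data are set against a "historical baseline generated by 66 patients who meet the study eligibility criteria" and who came before the study began.
- **Inference (same section).** The data are to "evaluate the impact that in-clinic use of the Trial Library tool has on the duration of each clinic visit". The test is a two-sample t test on mean minutes, introduced with the words "To evaluate if the Trial Library intervention increases clinic length time".

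The components of the intervention listed under Study intervention are educational content, the matching tool and the patient report. Consent and survey are not among them.

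**The concern.** The two groups differ by the tool plus the research procedures, but the difference is to be read as the effect of the tool alone. Consent and survey would not be part of routine use, so their minutes say nothing about whether the tool fits a clinic.

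The Abstract names visit duration as the feasibility measure. The Discussion names disrupted workflow and longer clinic time as the foreseeable risk that visit time is meant to capture. The pilot is also described as preliminary data for a multi-site randomized trial. An upward bias would make the tool look less workable than it is, and research minutes that are not recorded on the day cannot readily be separated later.

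**Working it through.** **No figure to reproduce.** The article gives no standard deviation, detectable difference, power, significance level or sidedness for this comparison.

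**Step 1: when research time lengthens the visit.** Write W for the wait a patient would have had anyway, c for introduction and consent, u for tool use, and s for survey minutes inside the RTLS interval. Suppose the provider is ready after W and waits for the patient if need be. The protocol puts consent before the tool, so:

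- minutes added with consent and tool: max(0, c + u − W), plus s;
- minutes added by the tool alone: max(0, u − W);
- bias = max(0, c + u − W) − max(0, u − W) + s.

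The bias is never negative. It is 0 if consent and tool both fit within the wait and the survey lies outside the interval. It reaches c + s if the tool alone already fills the wait. A tool that would fit within the wait by itself may overrun it because consent came first. The survey has no wait for the provider left to absorb it.

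**Step 2: what subtracting consent does.** With the survey excluded (s = 0), max(0, c + u − W) − c ≤ max(0, u − W) ≤ max(0, c + u − W). The unadjusted difference is therefore an upper bound for the tool's effect, and the difference after subtracting the whole consent period is a lower bound, as far as this source of bias goes.

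**Step 3: illustration of size.**

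From the document: n = 66 participants ("The sample size for this study is 66 participants") and 66 historical patients, so df = 66 + 66 − 2 = 130.

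Assumed: unabsorbed research minutes d = 5 to 20, SD = 20 to 60 minutes, significance level 0.05, true tool effect zero.

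Noncentrality = d / (SD × √(2/66)). Example: SD 30 gives a standard error of 30 × 0.1741 = 5.22; d = 10 gives 10 / 5.22 = 1.91. Against the two-sided critical value of t on 130 df, the rejection probability is 0.476.

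Rejection probability with no tool effect, two-sided (one-sided in brackets):

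| SD (min) | d = 5 | d = 10 | d = 15 | d = 20 |
|---|---|---|---|---|
| 20 | 0.297 (0.414) | 0.814 (0.887) | 0.990 (0.996) | 1.000 (1.000) |
| 30 | 0.158 (0.244) | 0.476 (0.603) | 0.814 (0.887) | 0.967 (0.985) |
| 45 | 0.097 (0.156) | 0.245 (0.354) | 0.476 (0.603) | 0.717 (0.815) |
| 60 | 0.076 (0.121) | 0.158 (0.244) | 0.297 (0.414) | 0.476 (0.603) |

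With d = 0 (full absorption, or research time removed) the rate is 0.05.

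**The case against.** The strongest reply has four parts.

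1. **The RTLS interval is not defined**, and a condensed article may leave such detail to the full protocol. The survey is called post-visit, and the moment of the HIPAA form is not stated. This stands: a reader might infer that the recorded duration certainly contains consent, form and survey, and the document does not say so. What remains is that the article itself states the contrast and attributes it to the tool, while consent clearly takes place in clinic after check-in.
2. **Consent may use time that historical patients spent waiting idle.** This stands too, and is why the bias from consent can be as low as zero. It does not cover the survey, if the clock is still running then.
3. **Length with provider contains none of these steps.** Correct. It does not follow that provider time should become the lead measure. The tool is used after check-in on an iPad, so provider time would miss the waiting-room use that the comparison is meant to assess.
4. **Little hangs on the result.** Feasibility is exploratory, has no threshold, and is also judged from interviews with 10–12 patients and 6 physicians. This limits the consequence: no rule lets the t test alone declare the tool unworkable, and the article does not say that a duration estimate will be carried into the randomized trial. The difference is still to be reported as the tool's impact.

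**Conclusion.** The point holds in a limited form. As written, the comparison mixes research time with tool time, and this component of bias can only run upward, against the tool, in total visit duration or wait time. Its existence depends on research minutes lying inside the recorded interval and not being absorbed by waiting.

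Its size is unknown. Over the assumed ranges the two-sided false-positive rate runs from about 0.08 to near 1, and it is 0.05 under full absorption. A reader might take one row of the table, such as 0.48 to 0.81 for 10 to 15 minutes at SD 30, as the expected error rate. The document supports neither those minutes nor that SD. The correction is worth making because it is cheap and must be in place before data are collected, not because a large bias has been shown.

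**What to change.** In the RTLS paragraphs of the section Qualitative semi-structured interview:

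1. Define the start and end of the RTLS visit interval for both groups, with the participants' interval ending before the post-visit survey.
2. Time-stamp consent start, iPad hand-over, iPad return and survey start. Say whether the HIPAA form falls within the consent period.
3. Report tool time (hand-over to return) and research time (consent start to hand-over, and survey) separately.
4. Compare wait time and total visit with the historical group twice, with and without subtracting the consent period, and present the two results as bounds. Subtraction alone would over-correct wherever consent used idle waiting, and would then favour the tool.
5. Keep total visit duration as the feasibility measure, and report time with provider beside it as the component free of research steps.

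The cost is four time stamps per participant, plus a wording change. Front-desk staff may have to record some of them, since the iPad is returned there. The result will be a range and not a single corrected estimate.

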## Discussion

This novel study leverages health information technology to develop an online informational resource for a diverse patient population. The principles that informed the design of the Trial Library intervention aim to be generalizable to clinical trials across many disease contexts. From the ground up, this resource is built to be inclusive of the linguistic, literacy, and technological needs of underrepresented patient populations.

This study will measure the acceptability of the Trial Library intervention among patients with prostate cancer seen at one academic medical center. The qualitative component of this mixed methods study will capture the participant and physician experience with the intervention. This study will provide critical preliminary data prior to a larger multi-site randomized clinical trial of the intervention. Positive results from this study would support the use of Internet-based recruitment tools as a viable method for recruiting diverse patient populations into clinical trials within a clinical setting. Additionally, preliminary data from this study may inform larger interventions delivering online health information to improve clinical trial recruitment in the community.

This study will also examine the physician perspective after incorporating a patient online trial resource in the clinical context. Given that this intervention is being tested in a closed system, the clinic, we will be able to assess the impact of the intervention on the patient and physician clinical experience. It is possible implementation of this study intervention may disrupt workflow and increase clinic length. This study is targeting new patients and measuring clinic visit time to capture these effects.

We anticipate limitations in this single site pilot study and will only capture preliminary estimates of efficacy. The intervention will only populate one clinical site’s available trials and be available in English. Future studies will include a translated copy of the website in Spanish and incorporate trial options for multiple clinical sites.

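### The t test planned for visit length cannot by itself show that any added clinic time is acceptably small, and no acceptable increase is stated

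*Protocol article*

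**What the plan says.** Under Qualitative semi-structured interview, the article ranks the objective: "An exploratory objective of this study is feasibility". It then says what the objective draws on: "Feasibility will be measured through semi-structured interviews and clinical data, such as impact on duration of visit and wait time". Times come from the clinic's locating system, and of these the article says: "These measures will be used to assess the feasibility of this intervention". The comparator is a "historical baseline generated by 66 patients who meet the study eligibility criteria", seen before the study began. The analysis is introduced as "To evaluate if the Trial Library intervention increases clinic length time", and a two-sample t test "will be used to compare minute average of study participants with the reference group".

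The Methods part of the abstract describes feasibility by visit duration alone. The Discussion names the worry: "It is possible implementation of this study intervention may disrupt workflow and increase clinic length". It adds that visit time is measured in order to pick this up.

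Under Sample size and justification, "The sample size for this study is 66 participants". That number is justified only by the test of the satisfaction rate. Satisfaction is also given a point estimate, a 95% interval and a rejection rule. Visit length is given only the t test.

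**The concern.** The practical question is whether any extra time in clinic is small enough to live with. A test of no difference answers another question: whether the data are incompatible with zero increase. The reassuring outcome for the tool would be a failure to reject, and that becomes more likely as the data become noisier or fewer. A p-value above 0.05 therefore fits both no added time and an increase that the clinic would find unworkable. The opposite error is also possible: a small increase that happens to be significant could count against the tool although nobody would mind it.

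The pilot is meant to supply preliminary data for a multi-site randomized trial. For that purpose, an estimate of added minutes with its upper bound is more useful than a significance verdict.

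**Working it through.** **Inputs from the article.** Study group 66 (Sample size and justification); historical group 66 (Qualitative semi-structured interview); two-sample t test on mean minutes. For this comparison the article states no SD, increase of interest, acceptable increase, significance level, sidedness or power. There is therefore no figure of the plan's own to reproduce. The type I error and power that it prints belong to the satisfaction test.

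**Assumptions.** Significance level 5%, two-sided unless stated; equal SD in both groups; SD of 15 to 40 minutes, shown as a range.

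**Step 1: precision in SD units.** The standard error of the difference is SD × √(1/66 + 1/66) = SD × √(2/66) = 0.174 SD. With 130 degrees of freedom, the two-sided critical value is 1.978.
- Power is about 50% where the true increase equals the critical difference: 1.978 × 0.174 = 0.34 SD (one-sided: 0.29 SD).
- Power of 80% needs (1.960 + 0.842) × 0.174 = 0.49 SD (one-sided: 0.43 SD).
- Noncentral t power at 0.2, 0.3, 0.4 and 0.5 SD is 0.21, 0.40, 0.63 and 0.81 two-sided, and 0.31, 0.53, 0.74 and 0.89 one-sided.

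**Step 2: in minutes.** The 95% half-width is 1.978 × 0.174 × SD. Power is from the noncentral t at increase/SD.

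| Assumed SD (min) | 95% half-width (min) | Increase with 80% power (min) | Power for 5 min, two-sided (one-sided) | Power for 10 min, two-sided (one-sided) |
|---|---|---|---|---|
| 15 | 5.2 | 7.3 | 0.48 (0.60) | 0.97 (0.98) |
| 20 | 6.9 | 9.8 | 0.30 (0.41) | 0.81 (0.89) |
| 25 | 8.6 | 12.2 | 0.21 (0.31) | 0.63 (0.74) |
| 30 | 10.3 | 14.6 | 0.16 (0.24) | 0.48 (0.60) |
| 40 | 13.8 | 19.5 | 0.11 (0.18) | 0.30 (0.41) |

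**Step 3: the same data judged against an acceptable increase.** Take 10 minutes purely as an illustration, with true difference zero and one-sided 2.5%. The chance that the upper limit falls below 10 minutes is Φ(10/(0.174 × SD) − 1.96). This gives 0.97, 0.82, 0.63, 0.48 and 0.30 for SD 15, 20, 25, 30 and 40. For an 80% chance, the number needed per group would be 36, 63, 99, 142 and 252. On that illustration, 66 per group is enough at an SD of 20 minutes or less, and not at 25 or more.

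**The case against.** Four points weigh on the other side.

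1. A reader might infer that the protocol will take non-significance as proof of no disruption. Nothing in the article says so: it sets no such rule, and its Discussion openly allows that disruption may occur. This point stands. What remains is that the named analysis does not guard against that reading.

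2. A reader might infer that feasibility hangs on this one test. It does not. The article also plans interviews with 10 to 12 patients and all 6 physicians, and Table 2 links questions about the visit to feasibility. Wait time and time with the provider are collected too. The abstract's narrower description gives the stronger reading some colour, but the body text is the fuller statement. The objective is also exploratory, in a single-site pilot. This point stands and lowers the weight of the concern.

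3. A reader might infer that a real increase would probably be missed. Without an SD or an increase of interest, the documents cannot support that. It holds below about 0.34 SD. At 0.5 SD, two-sided power is about 81%, and at an SD of 20 minutes or less, a 10-minute increase would be detected with power of 0.81 or more.

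4. An interval for the difference, the form of the t test and its sidedness are details that an article may leave to a fuller document, and the same standard error yields the interval. That is fair, and their absence is not the point. The point is the stated choice: a test for an increase, applied to a question about acceptably small added time.

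**Conclusion.** The concern holds in a limited form. The only quantitative analysis named for visit length is a difference test with no acceptable increase to judge it by, at a sample size fixed for another endpoint. A non-significant result from it could not establish that added time is tolerable. The SD-unit results rest only on 66 per group, equal SDs and a 5% level; those in minutes depend on the assumed SD. Because the objective is exploratory and has other sources of evidence, this is a worthwhile, inexpensive improvement and does not invalidate the study.

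**What to change.** Reword the visit-length analysis so that its planned result is the mean difference in minutes between participants and the historical group, with a Welch confidence interval, which does not assume equal spread in the two periods. Have the investigators state the largest acceptable increase before anyone reviews the data. Interpret the upper confidence limit against that figure, together with the patient and physician interviews. If the limit lies above it, report that acceptably small added time has not been shown. State that p > 0.05 will not be treated as evidence of feasibility. The size of the acceptable increase is for the investigators and the clinic to decide.

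The cost is some analysis wording and one agreed number, with the same patients and the same locating-system data. There are two drawbacks. The result may be inconclusive, the more so the larger the SD. And the interval does not remove differences between the study period and the historical period, so it should be reported as a non-randomized comparison.
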